### Blinding

No one will be blinded before, during or after the trial as the realized rehabilitation program will be recognizable for all stakeholders.

### Data collection

Outcomes and other measures will be assessed with patient questionnaires or will be extracted from the rehabilitation discharge letters (see Table 2). For participants who do not complete follow-up questionnaires, missing data will be imputed. If participants withdraw their participation, the collected data will be deleted.

Three consecutive interviews with participants of the complementary panel study are planned. The first interviews will take place during rehabilitation in the rehabilitation centers as focus groups. After three and 12 months, follow-up interviews with the same sample will be conducted as individual interviews by telephone or video call. Furthermore, members of the multi-professional teams, team leaders and the respective medical directorate of each rehabilitation center will be interviewed. Again, the first interviews will be conducted in the rehabilitation centers and the second interview after 6 months by telephone or video call. The interviews of teams and team leaders will be conducted as focus groups.

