## Methods

### Study setting

Participants will receive either a WMR or CPR program in one of six rehabilitation centers located in Germany (Rehazentrum Oberharz in Clausthal-Zellerfeld, Reha-Zentrum Seehof in Teltow, Fachklinik Aukrug, Klinik am Hainberg in Bad Hersfeld, Celenus Parkklinik in Bad Bergzabern and MediClin Bliestal Kliniken in Blieskastel). The rehabilitation programs will be provided as inpatient programs. Participation was approved either by the Federal German Pension Insurance or a regional pension insurance agency. In both programs, interventions will be performed by rehabilitation physicians, psychologists, physiotherapists, sports therapists, social workers, occupational therapists and other health professionals.

The duration of the rehabilitation program is initially determined by the pension insurance agency (usually about 5 weeks). The rehabilitation center and the patient can agree on an extension of the program. By request, the patient may stop the rehabilitation program ahead of schedule.

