### Sample size estimation

In order to ensure a 20% increase in the proportion of rehabilitants with stable return to work per rehabilitation center (CPR: 40%; WMR: 60%; power: 80%; level of significance: 5%), an analysis sample of 194 persons (i.e. 97 persons per intervention arm) is necessary. Although we will use multiple imputations to perform an intention-to-treat analysis, we increase the sample size to compensate for the potential loss of participants during our follow-up assessments. This ensures sufficient power even if only complete cases are analyzed. Assuming a response rate of 65% after 1 year, we will recruit 300 patients per rehabilitation center. In a total sample of 1800 patients, a minimal difference of seven points can be detected. In a total sample of 1164 patients (response rate of 65%), a minimal difference of eight points can be detected (Fig. 1).

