### Allocation

A separate randomization sequence is created for each rehabilitation center by the University of Lübeck. For the computer-generated randomization lists, blocks of four and eight are combined in order to guarantee balanced case numbers, even if the lists cannot be processed completely. The randomization envelopes are sealed and will be opened in the rehabilitation centers after informed consent of the participants is determined. After arriving at one of the six study centers, the potential study participants are informed in detail about the study, both orally and in writing, and are asked to participate by the study assistants, who have been trained by the research team. In particular, the potential participants are informed that there will be two different study groups (intervention group and control group) and that allocation to the two groups will be randomized.

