### Statistical methods

#### Treatment effect

We use random-effects models to take into account that different true effects are possible in different rehabilitation centers. Linear models will be used for continuous outcomes and logistic models for binary outcomes. Baseline scores of outcomes will be included as covariates. Possible differences in effects at the level of the rehabilitation centers may be associated with WMR or CPR implementation. In order to test an effect modification due to the implementation of either WMR or CPR, subgroups are formed based on the received treatment dose (content, consistency, achievement of objectives) and the work-related treatment dose delivered. To reduce the number of subgroup analyses, the mean differences between WMR and CPR for dose delivered and dose received are used to categorize the subgroups (high distinguishability vs. low distinguishability). We assume that greater distinguishability of both interventions based on treatment dose delivered and received is associated with higher effects. Further characteristics of the rehabilitation centers for subgroup analyses may derive from the focus groups. Gender, age, migration background and education are examined as possible moderating patient characteristics. Multiple imputations will be used to fill in missing data and to perform an intention-to-treat analysis.

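### Deleting the data of participants who withdraw after randomisation conflicts with the promised intention-to-treat analysis by multiple imputation

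*Protocol article*

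**What the plan says.** The Data collection section of the protocol article sets two rules, one after the other. For non-response: "For participants who do not complete follow-up questionnaires, missing data will be imputed". For withdrawal: "If participants withdraw their participation, the collected data will be deleted". The second rule has no time limit and does not exempt data gathered before the withdrawal.

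The analysis is described in two places. Sample size estimation has "Although we will use multiple imputations to perform an intention-to-treat analysis", and Treatment effect has "Multiple imputations will be used to fill in missing data and to perform an intention-to-treat analysis". Neither excepts withdrawn patients. Treatment effect also makes baseline scores of the outcomes covariates in the models.

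Three further statements matter:

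- Allocation: the randomisation envelopes "will be opened in the rehabilitation centers after informed consent of the participants is determined".
- Blinding: "No one will be blinded before, during or after the trial".
- Study setting, on ending treatment rather than study participation: "By request, the patient may stop the rehabilitation program ahead of schedule". No deletion is attached to this.

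**The concern.** Imputation under intention to treat needs a record for every randomised patient: at least the arm, and in practice the baseline covariates. A non-responder still has that record. A participant whose collected data are deleted has no baseline questionnaire, no discharge-letter data and no partial follow-up, and so drops out of the imputation model altogether. The set analysed becomes the patients who were randomised and did not later withdraw, which is a selection made after allocation.

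Withdrawal can follow knowledge of the arm, because consent precedes the opening of the envelope and nobody is blinded. If those who leave differ in prognosis, and do so differently between the arms, the comparison of return to work is biased. Once their baseline data are gone, the trial cannot describe who left or adjust for it.

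**Working it through.** **1. The two rules side by side**

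| Event after randomisation | What the article says | Available for imputation? |
|---|---|---|
| Follow-up questionnaire not returned | Imputed | Yes |
| Programme stopped early | Allowed, no deletion stated | Yes |
| Participation in the study withdrawn | Collected data deleted | No |

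Only the third row conflicts with the intention-to-treat promise.

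**2. The plan's own figures**

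Inputs from Sample size estimation: 40% against 60%, power 80%, level 5% (taken as two-sided), 65% response, 300 patients per centre, 1800 in total.

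n per arm = [1.96 × √(2 × 0.5 × 0.5) + 0.8416 × √(0.4 × 0.6 + 0.6 × 0.4)]² / 0.2² = (1.386 + 0.583)² / 0.04 = 96.9, so 97 per arm and 194 per centre, as stated.

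194 / 0.65 = 298.5, so 299 per centre against the stated 300.

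The detectable difference from 40% at 80% power is 6.5 points with 900 per arm (stated: 7) and 8.1 points with 582 per arm (stated: 8). The point therefore rests on no arithmetic error in the plan.

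**3. Records lost**

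The article gives no withdrawal rate. I assume 2% to 10%. Of 1800 records, 1764 remain at 2%, 1710 at 5% and 1620 at 10%.

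**4. Bias from deletion (illustrative)**

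Let p be the arm's true return-to-work rate, w the share withdrawn and q the return-to-work rate among those withdrawn. The rate among those retained is (p − w·q) / (1 − w). Take no true effect (p = 40% in both arms), 900 randomised per arm and everyone else observed. Bias is WMR minus control. Type I error is from a pooled two-proportion z test at a nominal 5%.

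| Control: w, q | WMR: w, q | Retained, control | Retained, WMR | Bias (points) | Type I error |
|---|---|---|---|---|---|
| any w, 40% | any w, 40% | 40.0% | 40.0% | 0 | 5.0% |
| 10%, 60% | 10%, 60% | 37.8% | 37.8% | 0 | 5.0% |
| 2%, 60% | 2%, 40% | 39.6% | 40.0% | +0.4 | 5.4% |
| 5%, 60% | 2%, 40% | 38.9% | 40.0% | +1.1 | 7.3% |
| 10%, 60% | 5%, 40% | 37.8% | 40.0% | +2.2 | 15.3% |
| 10%, 20% | 5%, 40% | 42.2% | 40.0% | −2.2 | 15.1% |

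For example, in the fourth row the control rate is (0.40 − 0.05 × 0.60) / 0.95 = 0.37 / 0.95 = 38.9%, and the WMR rate is (0.40 − 0.02 × 0.40) / 0.98 = 40.0%.

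A quick form of the same result is the excess withdrawal share times the outcome gap between those withdrawn and the rest of the arm (the same gap in both arms): 0.03 × 10 = 0.3 points, 0.05 × 20 = 1 point, 0.10 × 30 = 3 points.

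These values are not a ceiling. If 10% withdrew in each arm with opposite selection (q = 60% in control, 20% in WMR), the retained rates would be 0.34 / 0.90 = 37.8% and 0.38 / 0.90 = 42.2%, a bias of 4.4 points. That needs heavy withdrawal and strong, opposed selection together, and nothing in the article points to it.

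**The case against.** The strongest reply is that the rule may touch few people. The only loss the article quantifies is non-response (65% response at one year), and imputation covers it. If hardly anyone formally withdraws after randomisation, the analysed set is close to all randomised patients. This stands, and it limits the size of the problem. It does not reconcile the two statements.

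A reader might infer three stronger things that the article does not support:

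- *That the intention-to-treat analysis cannot be done.* Non-responders and patients who only stop the programme stay in it. The conflict concerns study withdrawal after randomisation, and with no such withdrawals the set is intact.
- *That patients are removed by arm.* The rule is the same for both arms. Loss that depends on arm is plausible without blinding, but it is a risk and not something the article states.
- *That the effect cannot be bounded.* The outcome is binary, so bounds need only the numbers randomised and erased in each arm. The article speaks of collected data and does not say that randomisation lists or allocation counts are destroyed. It also does not say that they are kept.

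Deletion may also be a condition of consent or data protection. The consent form is not available and the article condenses a fuller protocol, so this cannot be judged here. It is no bar to the repair, which still honours every request for erasure and changes only the default.

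**Conclusion.** The conflict is real and lies in what the article states, not in a detail left to another document. For patients who withdraw from the study after randomisation, automatic deletion is incompatible with intention to treat by multiple imputation. The bias is 0 if withdrawal is unrelated to outcome, or if the share and the outcome of those withdrawn are the same in both arms. Otherwise it is about 2 to 3 points at the upper end of the illustrative range, against a detectable difference of 7 to 8 points. The direction is unknown: losing controls with good prospects inflates the WMR effect, and losing controls with poor prospects understates it. All these sizes rest on assumed withdrawal rates and outcomes. Severity: should fix, because the likely bias is modest or nil, but deleted data cannot be recovered at analysis and the remedy is cheap.

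**What to change.** Replace the sentence in Data collection with: *Data collected up to withdrawal are retained and analysed in the randomised arm, with later outcomes imputed, unless the participant explicitly asks for deletion.* Match the consent form to it, so that ending further participation and asking for erasure are separate choices.

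For those who do ask for erasure, keep the allocation record or an anonymous count by arm and centre. Report the count in the participant flow, and add a sensitivity analysis that bounds the primary result over the possible outcomes of the erased patients. If any records are erased, describe the analysis set as all randomised patients except those erased.

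The cost is a small protocol and consent amendment with ethics approval. No extra patients or visits are needed and the sample size does not change. Participants already enrolled stay under the consent they signed, so the gain is larger the earlier the change is made.

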### Data management

Questionnaires will be entered manually into an electronic database by trained research assistants at the University of Lübeck. Data on the documented therapeutic dose are taken from the rehabilitation discharge letters and will also be entered into the electronic database. All personal data will be removed and replaced by the unique study identifier by the rehabilitation centers.

Recordings from the focus groups and interviews will be transcribed by trained assistants at Nordhausen University of Applied Sciences. The names of patients and staff will be pseudonymized during the transcription process. These pseudonyms will be added to the study list. Finally, questionnaire, administrative and qualitative data can be linked by the unique study identifier. Data management will be carried out by the authors of the protocol. Data access is limited to the authors and to the research assistants in the research team.

### Statistical methods

#### Treatment effect

We use random-effects models to take into account that different true effects are possible in different rehabilitation centers. Linear models will be used for continuous outcomes and logistic models for binary outcomes. Baseline scores of outcomes will be included as covariates. Possible differences in effects at the level of the rehabilitation centers may be associated with WMR or CPR implementation. In order to test an effect modification due to the implementation of either WMR or CPR, subgroups are formed based on the received treatment dose (content, consistency, achievement of objectives) and the work-related treatment dose delivered. To reduce the number of subgroup analyses, the mean differences between WMR and CPR for dose delivered and dose received are used to categorize the subgroups (high distinguishability vs. low distinguishability). We assume that greater distinguishability of both interventions based on treatment dose delivered and received is associated with higher effects. Further characteristics of the rehabilitation centers for subgroup analyses may derive from the focus groups. Gender, age, migration background and education are examined as possible moderating patient characteristics. Multiple imputations will be used to fill in missing data and to perform an intention-to-treat analysis.

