#### Received dose of work-related treatment components

To assess the fidelity of our intervention according to the patients treated, we will employ a slightly modified version of a previously used set of items from a study that investigated the nationwide implementation of the WMR guidelines in patients with musculoskeletal disorders [42]. Participants report on 12 binary items as to whether they received WMR content in their rehabilitation program. Scores are aggregated to a total score of 0–12 points. This score reflects the content of the work-related components. Additionally, six items assess the perceived consistency of the work-related approach (e.g. the experience of a coherent return-to-work strategy). These items are five-point graded and scores are summed to a total score of 0–24 points. Finally, the achievement of work-related goals will be assessed by eight items that are also five-point graded and scores are aggregated to a total score of 0–32 points.

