#### Delivered dose of work-related components

Therapeutic interventions will be extracted from the standardized rehabilitation discharge letters [44]. The documentation for the therapeutic interventions will indicate adherence to the WMR guidelines. The delivered intervention dose is also a potential effect modifier.

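### Grading centres by distinguishability partly on patients' goal achievement, a result of treatment rather than a dose, makes the planned implementation test partly circular

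*Protocol article*

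**What the plan says.** Statistical methods (Treatment effect) starts from differences between centres: "Possible differences in effects at the level of the rehabilitation centers may be associated with WMR or CPR implementation". To test this, "subgroups are formed based on the received treatment dose (content, consistency, achievement of objectives) and the work-related treatment dose delivered". To limit the number of subgroup analyses, "the mean differences between WMR and CPR for dose delivered and dose received are used to categorize the subgroups", giving a high and a low group. The direction expected is stated: "We assume that greater distinguishability of both interventions based on treatment dose delivered and received is associated with higher effects". A difference between arms exists only for a group of patients, so the units being graded are the centres.

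The third ingredient is defined under Received dose of work-related treatment components: "the achievement of work-related goals will be assessed by eight items that are also five-point graded", summed to 0 to 32 points. The stated purpose of the whole item set there is: "To assess the fidelity of our intervention according to the patients treated". The How well row of Table 1 says that patients are asked about content and goal achievement at the end of the program. The Blinding section says that nobody is blinded. The primary outcome is stable return to work at 12 months.

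**The concern.** Delivered dose, received content and perceived consistency describe the program. Achieving a work-related goal describes what the program led to. In a randomised trial, the difference between arms in such a score, taken after treatment, is itself a treatment effect. Here it is an early one, rated by patients who know their arm.

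A centre where WMR happens to work better, by chance or for reasons unrelated to how it was implemented, will tend to show a larger goal-achievement difference. That pushes it towards the high label. The return to work of the same patients is then compared between labels, and a larger effect in the high group is read as a consequence of implementation. An early effect that predicts a later one would produce the same pattern. What is at stake is the reading of this one effect-modification analysis.

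**Working it through.** **Inputs from the protocol.** Six centres; 40% versus 60% stable return to work; 80% power; 5% significance; 97 per arm per centre analysed; 65% response; 300 recruited per centre.

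**The protocol's own figures.** The two-sided formula for two proportions (pooled variance, no continuity correction) gives 97 per arm, 194 per centre, with power 80.0%. Then 194/0.65 = 298.5, rounded up to 299 (stated: 300), and 6 × 194 = 1164. These reproduce, and the point does not turn on them.

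**Assumptions, none of them in the protocol.** Patient-level correlation ρ of 0.3 to 0.5 between goal score and return to work; a 3 versus 3 split; the same true effect in every centre; four equally weighted, standardised ingredients, of which only goal achievement correlates with return to work; a true between-centre SD, τ, of 0, 0.2 or 0.4 in distinguishability, common to the ingredients.

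**Sampling error of one centre's arm difference.**
- Return to work: s_R = √(2 × 0.24/97) = 0.0703, that is 7.03 points.
- Any standardised score: s_G = √(2/97) = 0.1436 SD.

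**Spurious gap.** If six centres are ranked on an index whose correlation with the chance error in the return-to-work effect is c, the expected difference between the top three and the bottom three is c × s_R × k. Here k is the mean of the top three minus the mean of the bottom three of six standard normal values, about 1.407 by simulation. So the gap is c × 7.03 × 1.407 = c × 9.9 points.

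- Goal achievement alone: c = ρ × s_G/√(τ² + s_G²).
- Four equal ingredients: c = ρ × (s_G/4)/√(τ² + s_G²/4).

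Examples at ρ = 0.5:
- Alone, τ = 0: c = 0.5, gap 4.9 points.
- Four ingredients, τ = 0: c = 0.25, gap 2.5 points.
- Four ingredients, τ = 0.2: c = 0.5 × 0.0359/√(0.04 + 0.00515) = 0.084, gap 0.8 points.

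A simulation of 200,000 trials per setting agrees and adds the rejection rate of a 5% z-test of the high-minus-low difference:

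| Grading | τ | Gap, ρ = 0.3 to 0.5 (points) | Rejection |
|---|---|---|---|
| Four equal ingredients | 0 | 1.5 to 2.5 | 5.6 to 6.6% |
| Four equal ingredients | 0.2 | 0.5 to 0.8 | about 5% |
| Four equal ingredients | 0.4 | 0.3 to 0.4 | about 5% |
| Goal achievement alone | 0 | 3.0 to 5.0 | 7.3 to 11.8% |
| Goal achievement alone | 0.2 | 1.7 to 2.9 | 5.9 to 7.3% |

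**If true centre effects vary.** In a second simulation, true return-to-work effects varied between centres with an SD of 8 points, unrelated to dose, and true centre differences in goal achievement correlated 0.5 to 0.8 with them (ρ = 0.3, score SD 0.2). The spurious gap was 2.3 to 3.5 points at one-quarter weight and 6.3 to 9.1 points if goal achievement alone drove the grading. I do not use the rejection rates from this setting: the simple z-test ignores between-centre variance and rejects about 20% of the time even without goal achievement. That is a property of the test and separate from this point.

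**With goal achievement removed.** The gap is about 0 in both settings. With a constant true effect, rejection is about 5% at every ρ tried (0 to 0.6).

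**For scale.** With 3 × 97 = 291 per arm in each group, the gap detectable with 80% power is 2.80 × √(2 × 0.48/291) = 0.161, about 16 points.

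**The case against.** The strongest reply is that the size is modest. Goal achievement is one ingredient of four, the outcome tested is 12-month return to work and not goal achievement, and with real dose differences between centres the constant-effect bias at equal weights is under 1 point, against a detectable gap of about 16. This stands as to size. It does not change what the label means: a variable that responds to treatment success helps decide which centres count as well implemented.

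The protocol also presents the items as fidelity, in a subsection on received dose, and their wording is not shown. They might ask whether the program pursued work goals rather than whether the patient reached them. That cannot be excluded, but the protocol describes the score as achievement of goals. The position of the subsection under Secondary outcomes proves nothing either way, because the content score stands there too and is also patient-reported after randomisation. The case against goal achievement rests on what it measures.

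A reader might infer that the hypothesis is confirmed by construction, or that a false gap of 3 to 5 points is to be expected. The documents do not support this: those figures need goal achievement to be the only ingredient and centres not to differ truly in the score. A reader might also infer a heavily inflated type I error from patient-level testing that ignores centre variation. The protocol plans random-effects models because true effects may differ between centres, so that would be a hypothetical error. The limited power of a comparison across six centres affects any centre-level modifier and is a separate matter.

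**Conclusion.** The point holds as partial circularity. The grading mixes how distinctly the program was delivered with how well it worked, so a larger effect in high centres could not be attributed to implementation.

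Under the assumptions listed (ρ 0.3 to 0.5, 3 versus 3, constant true effect), the spurious gap is about 0.3 to 2.5 points at one-quarter weight, with rejection of about 5 to 7%. Its upper limit is 3 to 5 points and 7 to 12% if goal achievement alone drove the grading. It can be larger if true centre effects vary for other reasons and goal achievement follows them. The protocol states neither the weights nor the cut-off, so no single figure can be given.

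The primary hypothesis and the overall comparison of WMR with CPR are unaffected. A reader might infer that decisions on wider use of WMR depend on this subgroup result, but the document does not say so.

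**What to change.** Remove achievement of objectives from the grading. Define distinguishability from delivered dose, received content and perceived consistency. The protocol already names the first of these as a modifier: "The delivered intervention dose is also a potential effect modifier". Analyse goal achievement as an outcome, or as a mediator between treatment and return to work. Make the change before follow-up results are examined by centre.

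The cost is one fewer ingredient in the grading. All the data are already planned, and neither the sample size nor the primary analysis changes.

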### Trial design

The study is a randomized controlled trial with two parallel groups. Participants are randomly assigned to a WMR or CPR group in a one-to-one ratio. Focus groups and individual interviews supplement our study with qualitative data.

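### Splitting six measured centre dose contrasts into high and low distinguishability loses information in an already weak secondary test; a continuous moderator fits the stated hypothesis better

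*Protocol article*

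**What the plan says.** The trial randomises patients 1:1 within each of six centres (Study setting: "Participants will receive either a WMR or CPR program in one of six rehabilitation centers located in Germany"). Under Treatment effect, the article allows the true effect to vary by centre through random-effects models. It suggests that such variation may reflect how WMR or CPR was implemented.

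To test this, it forms subgroups from delivered dose and from three received-dose scores (content, consistency, achievement of goals). To limit the number of subgroup analyses, "the mean differences between WMR and CPR for dose delivered and dose received are used to categorize the subgroups", with two levels: high and low distinguishability. The expectation is then stated as a gradient: "We assume that greater distinguishability of both interventions based on treatment dose delivered and received is associated with higher effects".

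Under Delivered dose of work-related components, the article adds: "The delivered intervention dose is also a potential effect modifier". It does not say there in what form that would be analysed.

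**The concern.** The hypothesis is graded and the planned analysis is not. Each centre will have a measured WMR-minus-CPR difference in dose. Once the centres are split in two, a centre just above the cut counts the same as the centre with the largest contrast, and all dose variation within a class is ignored.

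The reason given, fewer subgroup analyses, does not require a split. One treatment-by-contrast term for a dose measure is one analysis, just as one high/low comparison is.

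What is at stake is interpretation. If the overall effect is small or uneven, this analysis would help to separate a programme that does not work from two arms that hardly differed in content. With only six centre-level values, there is little information to give away.

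**Working it through.** **1. The plan's own figures.** Sample size estimation takes 40% against 60%, 80% power and 5% significance (two-sided reproduces), and states "an analysis sample of 194 persons (i.e. 97 persons per intervention arm) is necessary".

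n per arm = [1.96·√(2·0.5·0.5) + 0.842·√(0.4·0.6 + 0.6·0.4)]² / 0.20² = (1.386 + 0.583)² / 0.04 ≈ 97.

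Then 194/0.65 ≈ 299, in line with "Assuming a response rate of 65% after 1 year, we will recruit 300 patients per rehabilitation center", and 6 × 194 = 1164. These figures reproduce. The article states no power for the dose-effect analysis, so there is no figure of its own to compare with what follows.

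**2. Information kept by a split.** If the effect is linear in the contrast, the share kept is the squared correlation between the contrast and the 0/1 class, that is, between-class sum of squares over total sum of squares. For six evenly spaced centres (0, 1, …, 5; mean 2.5), the total is 17.5.

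| Split | Class means | Between-class sum of squares | Share kept |
|---|---|---|---|
| 3:3 | 1 and 4 | 6 × 1.5² = 13.5 | 77% |
| 4:2 | 1.5 and 4.5 | 4 × 1² + 2 × 2² = 12 | 69% |
| 5:1 | 2 and 5 | 5 × 0.5² + 1 × 2.5² = 7.5 | 43% |

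For six contrasts drawn at random, the average shares by simulation are:

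| Distribution | 3:3 | Split at the mean | 5:1 |
|---|---|---|---|
| Normal | 66% | 75–76% | 45% |
| Uniform | 70% | 79% | 41% |
| Two clear clusters of three | 94% | 94% | 30% |

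For normal or uniform contrasts, the loss is therefore about 21–34% with a mean or 3:3 split and about 55–59% with a 5:1 split. It is about 6% when the split matches two real clusters.

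**3. Power.** Inputs from the article: six centres and 97 analysed per arm per centre. Assumed, because the article gives no figure: centre contrasts normal with SD 4 h, effect linear at 3 or 2 percentage points per hour, dose contrast measured without error, and no residual heterogeneity beyond dose.

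Standard error of one centre's risk difference = √(2 × 0.24/97) = 0.070.

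The six centre effects are regressed on the contrast or on the class, with two error models: (a) error known from patient-level sampling variance, z test; (b) error estimated from the scatter of the six centre effects, t test on 4 df. Under (b), dose variation left inside each class counts as error, so the split is penalised a second time.

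| Slope | Error model | Continuous | 3:3 split | Split at the mean |
|---|---|---|---|---|
| 3 points/h | (a) sampling variance | 86% | 75% | 79% |
| 3 points/h | (b) six centres, 4 df | 71–72% | 29–30% | 40% |
| 2 points/h | (a) sampling variance | 64% | 50% | 54% |
| 2 points/h | (b) six centres, 4 df | 45–46% | 21% | 27% |

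**4. How large these inputs are.** With SD 4 h, the range across six centres averages about 10 h. At 3 points per hour the true centre effects then span about 30 points, more than the 20-point effect that the article plans for. In a milder case, with evenly spaced centres and a 20-point span, the continuous term has about 65% power under (a) and about 43% on a 4-df t test with sampling-level error. Six centres is a severe limit before any split is made.

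**The case against.** The strongest reply is that the loss is easily overstated. A reader might infer that the split throws away most of the power. The documents do not support that. The fall to about 30% appears only when the error is estimated from six points. With sampling-variance error most of the power remains (86% to 75%). The article plans random-effects models and does not specify an unweighted regression on six centres, so its analysis could fall between these results. The slope and the SD of 4 h are assumptions. Error in the observed contrasts would also lower the power of the continuous version.

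Three other inferences go too far:

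- **That the cut is arbitrary.** The article states no cut, but the rule may sit in a fuller plan that is not shown.
- **That delivered and received dose are merged into one class.** The sentence can equally mean a separate high/low split for each.
- **That this is the trial's only possible dose-response test.** It is the only one whose form is given; delivered dose is also named as a potential modifier without a stated form.

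The alternative has limits too. One centre can drive a linear slope over six non-randomised centre contrasts, and if the centres form two clusters a matching split loses almost nothing.

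All of this stands, and it limits the size and weight of the point. It does not answer the mismatch between a graded hypothesis and a two-class analysis, or show that limiting the number of analyses calls for a split.

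**Conclusion.** The point holds in a moderate form. The article expects the effect to rise with the dose contrast but analyses the contrast as high versus low. For a linear relation, this costs roughly a quarter to a third of the information with a balanced or mean split and about 55–60% with a 1:5 split. It costs little if the centres form two clear groups.

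The power cost runs from about 11 points (86% to 75%) to about 42 points (72% to 30%) at 3 points per hour. At 2 points per hour it runs from 14 (64% to 50%) to about 25 (46% to 21%). Which end applies depends on how between-centre variance enters the model. These powers rest on the assumed SD, slopes, linearity and error-free dose contrasts.

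The analysis is secondary and weak with six centres under either coding. The primary comparison and the sample size are unaffected.

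**What to change.** In Statistical methods, Treatment effect, replace the high/low subgroup test with one treatment-by-dose-contrast term in the random-effects model. The moderator is the centre's WMR-minus-CPR difference in mean delivered work-related dose, entered as a continuous variable. Report the change in effect per unit of dose with its confidence interval, and plot the six centre effects against the contrast. Analyse received dose as a separate secondary moderator. Keep high and low distinguishability only as a description of the centres.

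The cost is a few sentences of wording and no new data, since both dose measures are already collected. The downside is a linearity assumption that six points can check only weakly and that a single centre can drive. The plot and the confidence interval make that visible, and the result should be presented as exploratory.
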